## Missing Data

No replacement of missing data will be performed and the affected measurements will be regarded as lost for final statistical analysis.

## Demographic Data

Demographic variables (e.g. age, gender, BMI) will be given for each defined analysis population. Data will be summarized using frequency distributions (number and percentage) for categorical/ordinal variables and mean, standard deviation and range for continuous variables.

|                                                                                                                    |              |                         |                  |                    |
|--------------------------------------------------------------------------------------------------------------------|--------------|-------------------------|------------------|--------------------|
| Title: Clinical Investigation Plan                                                                                 |              | Author: [name] |                  | Philips restricted |
| DocID: ICBE-2-36455                                                                                                | Version: 3.0 | Date: 2020-DEC-08       | Status: Approved | Page: 33 of 44     |
| This document is based on Philips Research Template: Clinical Investigation Plan, ID: QR-TEM-57, Date: 2019-Mar-21 |              |                         |                  |                    |

### Expected drop-out rates

The expected drop-out rate is 10% (20 patients in this sample). Patients dropping out during the first 2 days of the study will be replaced until the final 200 patients are included and have participated more than the 2 days defined for replacement.

### Pass/fail criteria

The study is considered successful if the primary endpoint is addressed and the non-inferiority of outpatient recovery compared to regular treatment for bariatric surgery can be concluded.

### Interim analysis

The interim analysis will take place when data from 50 patients in both groups has been collected. Interim analysis will involve a comparison of the textbook outcome, as described above for the primary endpoint, between the two groups. The individual parameters of the textbook outcome will also be compared, i.e. discharge as planned, readmission in the 30 days after surgery, additional consultation by phone in the 7 days after surgery, additional consultation in the 7 days after surgery, and patient satisfaction. Based on the outcome of this interim analysis the investigators together with the sponsor will decide if the study needs to be stopped.

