| Brief Summary of Study

Provide a lay-language abstract of your study plan (100-300 words)
https://humansubjects.stanford.edu/new/docs/glossary_definitions/lay_language.pdf | 
This clinical investigation is a single center patient preference trial in a tertiary hospital in the Netherlands, designed to compare the outcome of two different recovery paths after standard of care bariatric surgery. The difference between both recovery paths is that half of the patients will get the standard of care by staying one night in the hospital before returning home (group B), while the other half will receive a Healthdot directly after surgery and leave the hospital on the same day (evening) (group A). 200 patients will be recruited and can choose whether they want to be assigned to the regular recovery path or receive a Healthdot and leave the hospital on the same day. If they have no preference they will be randomly assigned to one of the two groups. Patients in the outpatient recovery group will wear the Healthdot for 7 days at home and vital signs (heart rate and respiratory rate, together with context data on activity and posture) will be transmitted to the hospital to monitor recovery. The study is mainly designed to investigate if the clinical outcome in both groups is equal (non-inferiority) based on a combined outcome measures like 30 days readmission rate and patient satisfaction.
 |                                                                  |                                                                 |                                                                  |

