## Statistical design

This study is primarily designed to test for non-inferiority of outpatient recovery compared to regular treatment for bariatric surgery. The outcome measure that we will use for the analysis is a combined measure, based on the following:

- Mortality
- Severe postoperative complications (Clavien-Dindo IIIb or higher)
- Readmission (at least one night in hospital)
- Mild complications (Clavien-Dindo II and IIIa)
- Prolonged length of stay (3 days or more in hospital)

within 30 days after primary surgery.

We choose to use this combined outcome measure since it is in line with other surgical studies [5] making it comparable to literature.

I current practice at Catharina Hospital, Eindhoven, 95% of all bariatric surgery patients do not have any of these events which is considered the textbook outcome here.

We set the following null and alternative hypotheses for proving non-inferiority:

$H_0: p_{\text{regular}} - p_{\text{outpatient}} \geq \Delta$

$H_1: p_{\text{regular}} - p_{\text{outpatient}} < \Delta$

Where  $p_{\text{regular}}$  is the textbook outcome proportion in the regular treatment group, and  $p_{\text{outpatient}}$  is the textbook outcome proportion in the outpatient recovery group. We will use a non-inferiority margin ( $\Delta$ ) of 7%, which is deemed clinically significant by the Principal Investigator. This is also justified by a previous study where the average textbook outcome across bariatric surgery patients in the Netherlands was 88,7% [5] which helps to derive a non-inferiority margin of around 7% to the one seen at Catharina Hospital. We will use an uncorrected chi-squared statistic. Based on the sample size calculation done below an p value of 0.05 will be considered statistically significant. For the interim analysis an alpha correction for multiple testings is applied and a p value of 0.025 will be considered statistically significant.

The secondary endpoints will be analysed statistically in analogy to the primary endpoint by uncorrected chi-squared statistic where deemed appropriate.

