### Termination of entire study on statistical grounds

Based on the interim analysis, the study could be stopped in case of unacceptable inferiority or unanticipated accumulation of adverse events increasing patient risks to an unacceptable level.

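### The interim component breakdown lists items that, apart from readmission, are not components of the textbook outcome, and it names neither death nor complications

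*Protocol*

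**What the plan says.** Section 7, Statistical design, builds the combined measure from five events within 30 days of surgery: death; "Severe postoperative complications (Clavien-Dindo IIIb or higher"; readmission of at least one night; Clavien-Dindo II and IIIa complications; and a hospital stay of 3 days or more. It adds that at the study hospital "95% of all bariatric surgery patients do not have any of these events which is considered the textbook outcome here". Section 5 (Primary hypotheses) and section 6.1 (primary endpoint) give the same five events. A later paragraph of section 6.1 says all five are to be taken from the medical record.

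The Interim analysis section first calls for a between-group comparison of the textbook outcome as defined for the primary endpoint. It then says: "The individual parameters of the textbook outcome will also be compared, i.e. discharge as planned, readmission in the 30 days after surgery". The rest of that sentence names telephone consultations and other consultations beyond the plan in the first 7 days, and patient satisfaction. The investigators and the sponsor decide on stopping from this analysis. The section on termination on statistical grounds says that "the study could be stopped in case of unacceptable inferiority", or for an unanticipated accumulation of adverse events.

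The lay summary in section 1 describes the comparison as "based on a combined outcome measures like 30 days readmission rate and patient satisfaction".

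**The concern.** The Interim analysis section introduces its list with an i.e., so it reads as a statement of what the components are, not as a set of examples. That statement does not agree with the definition given everywhere else.

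What is at stake is how readable the interim is. The composite gives a death and a 3-day stay the same weight. With few events at this look, those deciding whether to continue need to see which kind of event occurred in which group. Followed as written, the breakdown would show satisfaction and consultation counts under the name of the textbook outcome, with no line for death or for either grade of complication.

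**Working it through.** This is mainly a comparison of texts.

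**Step 1. Match the lists.**

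| Primary endpoint component (sections 5, 6.1, 7) | Named in the interim list? |
|---|---|
| Death | No |
| Clavien-Dindo IIIb or higher | No |
| Readmission of at least one night | Yes, without the one-night condition |
| Clavien-Dindo II and IIIa | No |
| Stay of 3 days or more | Not named; loosely covered by planned discharge |

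| Interim list item | Endpoint component? |
|---|---|
| Discharge as planned | No, broader than prolonged stay |
| 30-day readmission | Yes |
| Additional telephone consultation, 7 days | No |
| Additional consultation, 7 days | No |
| Patient satisfaction | No, a secondary endpoint in section 6.1 |

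Overlap: 1 of 5. Listed items that are not components: 4 of 5. Components not named: 4 of 5, or 3 of 5 if planned discharge is accepted as a rough stand-in for prolonged stay.

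**Step 2. How good is that stand-in?** In Table 1 of section 6.4 the outpatient group is assessed for discharge at about 20:00 on day 1, and the regular group at about 12:00 on day 2. Any stay of 3 days or more therefore fails planned discharge in both groups. The reverse is not true: an outpatient kept for one night fails planned discharge without meeting the 3-day criterion. The item contains prolonged stay but is wider.

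**Step 3. Are the other items comparable between groups?** Section 6.4 gives the outpatient group a daily dashboard check on days 3 to 8, which may lead to a telephone call. The regular group has no appointments outside its usual protocol. Dashboard-prompted calls can therefore arise in one group only. The day-2 teleconsultation is scheduled, so it need not count as additional.

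**Step 4. How many events will there be?** Expected failures per group = patients per group × (1 − textbook-outcome rate). The interim wording can mean 50 per group or 50 in total, so both are shown.

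| Patients per group | Rate 0.95 (Statistical design) | Rate 0.96 (Sample size) |
|---|---|---|
| 50 | 50 × 0.05 = 2.5 | 50 × 0.04 = 2.0 |
| 25 | 25 × 0.05 = 1.25 | 25 × 0.04 = 1.0 |

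**Step 5. Is there a numerical stopping boundary?** Statistical design sets a p value of 0.025 for the interim. Under the hypotheses stated there, a significant result supports non-inferiority. Neither the Interim analysis section nor the termination section turns this, or any other figure, into a boundary for unacceptable inferiority. The decision is a judgement on what is displayed.

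**Step 6. Is anything else affected?** No. The stated 97 per group reproduces from the plan's inputs with a one-sided α of 0.05: (1.645 + 0.842)² × 2 × 0.96 × 0.04 / 0.07² ≈ 96.9, rounded up to 97. It does not depend on the interim list.

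**The case against.** A reader might infer that the stopping decision rests on the wrong components, with deaths and re-operations out of sight. The protocol does not support that. The sentence before the list requires the full composite as defined for the primary endpoint, and that composite counts every omitted event. The list is an addition to it. Adverse-event accumulation is a separate stopping ground, and section 14 has all adverse events reported to the study manager. This objection stands, and it limits the point to the breakdown.

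A reader might also infer that the interim composite would be rebuilt from the listed items, so that its rate no longer relates to the 95% figure or the 7-point margin. The reference back to the primary endpoint excludes that.

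Nor does the lay summary create a rival primary endpoint. It is an illustrative sentence in an abstract, and satisfaction appears among the secondary objectives in sections 1 and 5 and the secondary endpoints in section 6.1. It is loose wording that happens to err in the same direction as the interim list.

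Finally, planned discharge can be judged against each group's own plan, so it need not differ by design. That is fair. The objection is weaker for dashboard-prompted calls.

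One reservation remains about adverse events as a substitute. The Schedule of Activities marks adverse-event documentation up to day 8 and not at day 31, while the endpoint runs to 30 days. The adverse-event ground therefore only partly replaces a correct breakdown.

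**Conclusion.** The point holds in a limited form. The protocol contradicts itself on what the components of the textbook outcome are: four of the five items listed for the interim do not belong to it, and death and both complication grades are not named. The composite compared at the interim, the hypotheses, the margin, the sample size and the final analysis are not touched.

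The consequence is an interim breakdown that would not show which component drives a difference, and that mixes in items which are not endpoint components. This matters because the decision has no numerical boundary and only about 1 to 2.5 failures per group are expected. That range assumes a textbook-outcome rate of 0.95 or 0.96 and 25 or 50 patients per group.

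This is an internal inconsistency that should be corrected before the interim. It is not a flaw that invalidates the design.

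**What to change.** In the Interim analysis section, replace the list with the five components from Statistical design, tabulated by group. Report discharge as planned, additional consultations and patient satisfaction in a separate table, labelled as secondary or process measures that are not components of the textbook outcome. In the section 1 lay summary, describe the combined outcome by the same five components and mention satisfaction as a secondary measure.

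The cost is an amendment of wording. Section 6.1 already has all five components taken from the medical record, so no new data, patients or change in sample size are needed.

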### Termination of entire study on statistical grounds

Based on the interim analysis, the study could be stopped in case of unacceptable inferiority or unanticipated accumulation of adverse events increasing patient risks to an unacceptable level.

## 8 DATA MANAGEMENT

### Electronic Case Report Forms

An eCRF will be used in this study and will be completed for each included subject. The eCRF used for this study is Research Manager, a standard tool used by the clinical site for all clinical investigations.

The investigator has ultimate responsibility for the collection and reporting of all clinical, and safety data entered on the eCRFs and any other data collection forms (source documents) and ensuring that they are accurate, authentic/original, attributable, complete, consistent, legible, timely (contemporaneous), enduring and available when required. The eCRFs must be (electronically) signed by the Principal Investigator or the assigned subinvestigator to attest that the data contained on the eCRFs is true. Any corrections to entries made in the eCRFs, source documents must be dated, initialed and explained (if necessary) and should not obscure the original entry. In case of electronic data record, the corrections history will be maintained by an audit trail.

In most cases, the source documents are the hospital's or the physician's subject chart. In these cases data collected on the eCRFs must match the data in those charts.

In some cases, the eCRF, or part of the eCRF, may also serve as source documents. In these cases, a document should be available at the investigator's site as well as at Philips and clearly identify those data that will be recorded in the eCRF, and for which the eCRF will stand as the source document.

### Procedures

|                                                                                                                    |              |                         |                  |                    |
|--------------------------------------------------------------------------------------------------------------------|--------------|-------------------------|------------------|--------------------|
| Title: Clinical Investigation Plan                                                                                 |              | Author: [name] |                  | Philips restricted |
| DocID: ICBE-2-36455                                                                                                | Version: 3.0 | Date: 2020-DEC-08       | Status: Approved | Page: 34 of 44     |
| This document is based on Philips Research Template: Clinical Investigation Plan, ID: QR-TEM-57, Date: 2019-Mar-21 |              |                         |                  |                    |

The code list, signed informed consent forms and contact information will stay at the hospital. Coded data will be transferred to a Philips project share.

### **Data retention**

Personal data that will stay at the hospital will have a retention time of 15 years. Data stored on the Philips project share will be reviewed at least every 5 years for further retention.

## **9 AMENDMENTS**

Any changes to the clinical study protocol after initial ICBE approval are documented as protocol amendments. After ICBE approval, and prior to execution at the study site, the amendment will be:

- submitted and approved by the applicable IRB/REC and regulatory authorities
- signed by the Investigator(s)

## **10 DEVIATIONS**

Protocol deviations are any alteration or deviation from the ICBE-approved research plan as defined in the study protocol. This includes equipment failures during study procedures. The researcher will deviate from the protocol whenever necessary to protect the participant's health, rights or welfare and these types of deviations will be reported to ICBE and the external METC as soon as possible. Major deviations must be reported to ICBE and the external METC as soon as possible. In non-urgent/emergent situations, the researcher will obtain ICBE-approval for the planned deviation in advance of performing the changed activity.

If the researcher anticipates that there will be future requests for the same deviation, then the protocol will be amended (and such amendments must be approved by ICBE and the METC). A minor deviation is something that does not cause harm or have the potential to cause harm to the participant, and does not impact the integrity of the study. These shall be documented in the study file and uploaded to ICBE for their awareness. Other reasons for amendment requests include adding a study site, increasing the number of research participants, and extending the time to perform the study. If the study objectives and procedure or cohort changes or the study changes from non-medical to medical, this generates a new study (not an amendment).

### **Corrective and preventive actions and principal disqualification criteria**

All protocol deviations will be documented and assessed. If required, corrective and preventive action will be agreed upon and implemented with the relevant site. These decisions, activities and possible preventive actions will be documented.

A Principal Investigator can be disqualified if he/she has repeatedly or deliberately failed to comply with the requirements as specified in the protocol, including compliance with the relevant regulations, or if he/she has submitted false information in any required report.

Corrective actions may include supplemental protocol training, discussions with PI and study staff for activities to prevent future recurrence, etc.. Misconduct can cause PI disqualification.

## **11 DEVICE ACCOUNTABILITY**

The procedures for the accountability of investigational devices are in accordance with the Guidance.

|                                                                                                                    |              |                         |                  |                    |
|--------------------------------------------------------------------------------------------------------------------|--------------|-------------------------|------------------|--------------------|
| Title: Clinical Investigation Plan                                                                                 |              | Author: [name] |                  | Philips restricted |
| DocID: ICBE-2-36455                                                                                                | Version: 3.0 | Date: 2020-DEC-08       | Status: Approved | Page: 35 of 44     |
| This document is based on Philips Research Template: Clinical Investigation Plan, ID: QR-TEM-57, Date: 2019-Mar-21 |              |                         |                  |                    |

The access to investigational devices will be controlled and the investigational devices will only be used in the clinical investigation and according to the CIP.

The sponsor shall keep records to document the physical location of all investigational devices from shipment of investigational devices to the investigation sites until return or disposal. This record will be based on device accountability form.

The principal investigator or an authorized designee shall keep records documenting the receipt, use, return and disposal of the investigational devices. This record shall include:

- the date of receipt,
- identification of each investigational device (batch number/serial number or unique code),
- the expiry date, if applicable,
- the date or dates of use,
- subject identification,
- the date on which the investigational device was returned/explanted from subject, if applicable, and
- the date of return of unused, expired or malfunctioning investigational devices, if applicable.

Devices and/or questionnaires will be returned by the patient in a provided envelope to the hospital. The devices will be wiped down with standard alcohol wipes and will be quarantined together with the questionnaire for 4 days at the hospital before return to Philips (Covid-19 measure).

## 12 STATEMENTS OF COMPLIANCE

The clinical investigation will be conducted according to the principles of the Declaration of Helsinki and other guidelines, regulations and Acts. The study will be conducted in accordance with the Medical Research Involving Human Subjects Act (WMO) and the ISO 14155 standard on Clinical investigation of medical devices for human subjects — Good clinical practice.

The clinical investigation shall not begin until the required approval/favorable opinion from ICBE and the METC and regulatory authority have been obtained. Any additional requirements imposed by ICBE and the METC or regulatory authority shall be followed.

### Compensation for injury

Insurance for subjects participating in medical research that falls within the scope of the *WMO* is available in accordance with the legal requirements of article 7 of the *WMO* and *Medical Research (Human Subjects) Compulsory Insurance Decree* of 23 June 2003.

The sponsor/investigator has a liability insurance in accordance with article 7, subsection 6 of the *WMO*.

The sponsor (also) has an insurance in accordance with the legal requirements in the Netherlands (Article 7 *WMO* and the *Measure Regarding Compulsory Insurance for Clinical Research in Humans* of 23th June 2003). This insurance provides cover for damage to research subjects through injury or death caused by the study.

- € 650.000,-- (i.e. six hundred and fifty thousand Euro) for death or injury for each subject who participates in the Research;

|                                                                                                                    |              |                         |                  |                    |
|--------------------------------------------------------------------------------------------------------------------|--------------|-------------------------|------------------|--------------------|
| Title: Clinical Investigation Plan                                                                                 |              | Author: [name] |                  | Philips restricted |
| DocID: ICBE-2-36455                                                                                                | Version: 3.0 | Date: 2020-DEC-08       | Status: Approved | Page: 36 of 44     |
| This document is based on Philips Research Template: Clinical Investigation Plan, ID: QR-TEM-57, Date: 2019-Mar-21 |              |                         |                  |                    |

- € 5000.000,-- (i.e. five million Euro) for death or injury for all subjects who participate in the Research;
- € 7.500.000,-- (i.e. seven million and five hundred thousand Euro) for the total damage incurred by the organization for all damage disclosed by scientific research for the Sponsor as 'verrichter' in the meaning of said Act in each year of insurance coverage.

The insurance applies to the damage that becomes apparent during the study or within 4 years after the end of the study.

